## Abstract

**Background:**

While the world has made much global progress toward the reduction of new HIV infections, HIV continues to be an important public health problem. In the face of constantly constrained resources, donors and grantees alike must seek to optimize resources and deliver HIV services as efficiently as possible. While there is evidence that management practices can affect efficiency, this has yet to be rigorously tested in the context of HIV service delivery.

**Methods:**

The present protocol describes the design of a cluster-randomized control trial to estimate the effect of management practices on efficiency. Specifically, we will evaluate the impact of an intervention focused on improving management practices among community-based organizations (CBOs), on the costs of HIV prevention services for female sex workers (FSW) in Nigeria. To design the intervention, we used a qualitative, design thinking-informed methodology that allowed us to understand management in its organizational context better and to develop a user-centered solution. After designing the suite of management tools, we randomly assigned 16 CBOs to the intervention group, and 15 CBOs to the control group. The intervention consisted of a comprehensive management training and a management “toolkit” to support better planning and organization of their work and better communication between CBOs and community volunteers. Both treatment and control groups received training to record data on efficiency—inputs used, and outputs produced. Both groups will be prospectively followed through to the end of the study, at which point we will compare the average unit cost per FSW served between the two groups using a quasi-experimental “difference-in-differences” (DiD) strategy. This approach identifies the effect of the intervention by examining differences between treatment and control groups, before and after the intervention thus accounting for time-constant differences between groups. Despite the rigorous randomization procedure, the small sample size and diversity in the country may still cause unobservable characteristics linked to efficiency to unbalanced between treatment and control groups at baseline. In anticipation of this possibility, using the quasi-experimental DiD approach allows any baseline differences to be “differenced out” when measuring the effect.

**Discussion:**

This study design will uniquely add to the literature around management practices by building rigorous evidence on the relationship between management skills and practices and service delivery efficiency. We expect that management will positively affect efficiency. This study will produce valuable evidence that we will disseminate to key stakeholders, including those integral to the Nigerian HIV response.

*Trial registration* This trial has been registered in Clinical Trials (NCT03371914). Registered 13 December 2018

**Electronic supplementary material:**

The online version of this article (10.1186/s12962-018-0107-x) contains supplementary material, which is available to authorized users.

## Introduction

### Background and rationale

While over 19.1 billion USD in funding was available for the HIV response in low-and middle-income countries at the end of 2016 [1], HIV continues to be an important public health problem [2]. In 2016, there were 1.8 million new infections and 1 million AIDS-related deaths globally [1]. While treatment and transmission prevention programs have gone a long way to mitigate this, access to and retention in such programs—particularly in low-and middle-income countries—remain significant barriers to end the AIDS epidemic [3]. This is particularly true for so-called key populations, such as men who have sex with men, injection drug users, and female sex workers (FSW), for whom factors like stigma and discrimination pose additional barriers to receiving prevention and treatment services.

Nigeria is a lower middle-income West African country that suffers a generalized HIV epidemic—the second largest globally [4]. As of 2016, there were 3.2 million people infected with HIV, approximately a three percent prevalence [5]. While unprotected heterosexual sex is the main mode of transmission in the country, the epidemic is particularly concentrated in high-risk populations like FSW; the prevalence among brothel-based workers is estimated to be 14.4% [6]. FSWs are specifically targeted by current national efforts for HIV prevention, including the Minimum Prevention Package Intervention, or MPPI, which seeks to reduce the burden of HIV in key populations by providing a holistic suite of behavioral, biomedical, and structural components. Specifically, the package provides testing and counseling, peer education, sexually transmitted infection (STI) treatment, and community mobilization and advocacy [7].

Given the high burden of HIV in key populations and persistent funding scarcity, strategic investment that maximizes results is a priority for governments and funding agencies [8]. Therefore, programs increasingly prioritize efficiency—broadly defined as the economic value of resources spent relative to the number of goods or services produced and expressed by the average cost per service, or unit cost. Understanding unit costs delivered (a useful measure of efficiency) and cost drivers has become an essential aspect of optimizing service delivery. Management is a determinant of productivity in manufacturing [9, 10], and is widely accepted as a key factor of success in business. Recent research has translated this insight to the health sector, finding that management can affect health service delivery and outcomes in private care settings [11]. There is a paucity of evidence, however, about the relationship between management and healthcare outcomes in non-profit settings and in low-and middle-income countries. To address this gap, the National Institute of Public Health in Mexico, the Society for Family Health (SFH), and the National Agency for the Control of AIDS (NACA) in Nigeria, have partnered to design and implement the study, “Costs, efficiency and the role of management in HIV prevention interventions for Female Sex Workers in Nigeria”.

### Study objectives and hypothesis

The present study seeks to address two principal objectives:To measure the costs of implementing HIV prevention interventions and linkage to care services for FSWs in Nigeria; andTo experimentally evaluate the role of management practices on efficiency in community-based organizations (CBOs) in Nigeria.

We hypothesize that the intervention “package”—the data feedback, management training, and tools later described—will catalyze treatment sites to change key practices at their organizations, making service delivery more efficient.

### Trial design

This study is a cluster-randomized control trial (C-RCT) that examines the role of management practices on the costs of HIV services for FSWs in Nigeria. The project consists of two phases: (1) a design phase that uses qualitative methods to define and understand study population needs, and (2) an experimental phase, that implements a C-RCT. The design phase informed the content of a management intervention that will be implemented in CBOs and evaluated throughout the experimental phase.

## Methods

### Study setting and eligibility criteria

The study will collect and analyze efficiency data from CBOs across 14 states in Nigeria. To be included in this study, CBOs needed to (1) serve FSWs by providing HIV transmission prevention services, and (2) be funded through Society for Family Health (SFH) to offer services as part of the Global Fund or Strengthening HIV Prevention Services for Most at-Risk Populations (SHIPS for MARPs; USAID) grants. These sites offer counselling and testing, STI treatment, and HIV education services to brothels and hotspots in the surrounding area. All sites that met these criteria were included (n = 32).

### Intervention description

#### Phase I: Formative intervention design

To inform the creation of the management intervention, we employed qualitative methods to better understand the context of the CBOs. Participants were asked to fill 24 management journals, participate in 31 key informant interviews, and 6 non-participant observations at the CBO sites. Participants included managers and volunteers from CBOs in Nasarawa and Lagos states, and Abuja (the Federal Capital Territory, FCT). The study utilized a “design thinking” approach to define organizational needs and find opportunities for management solutions. Design thinking, borrowed from engineering and now often used in business and market research, is a method that uses empathy to understand the challenges and needs of a product’s “end user” in a specific context [12]. More similar to anthropology than other more prescriptive social sciences, it focuses on the user’s feelings, moods, desires, and latent needs. The phases of design thinking with respect to our project can be divided into distinct stages in which we: (1) “empathize” with the user, (2) “define” the issue, (3) “ideate” or brainstorm solutions, and (4) “prototype” possible solutions to challenges (Fig. 1).

**Fig. 1 Fig1:**

Timeline and stages of the intervention design

Journals were first distributed to CBO managers and they were asked to fill these out for 3–6 weeks prior to the start of the fieldwork (see Fig. 2). Managers were to describe their daily activities and detail challenges that they encountered in their work. We then reviewed the journals before fieldwork and scheduled interviews with stakeholders, which included NACA and SFH staff, officers working at the CBOs, and volunteers providing services (11 participants had filled the journals previously). During fieldwork, we then probed for more detail about the challenges they mentioned. In all interviews, participants were asked about their work, pertinent challenges, moments of particular difficulty, and topics that elicited strongest emotions. Finally, we conducted observations, during which we spent 2–6 h passively observing the landscape and interactions at a CBO. During their time at each site, we paid particular attention to interactions between managers and volunteers, as well as the physical surroundings that could affect program implementation.

**Fig. 2 Fig2:**
[figure not shown]
Design thinking cycle

From the information gathered through journals, interviews, and observations, salient themes were found across the data—including meeting targets, funding constraints, and complications in transportation and communication. We delineated patterns, and used these to reveal “insights”. In design thinking, insights are design-ready statements that capture the latent needs or “pain points” of the user, for which we design a solution. For example, researchers found that program officers were very focused on and concerned about meeting productivity targets. While they understood the need to monitor field activities, they found the transportation and scheduling of supervision challenging, due to competing priorities. Ultimately, officers struggled to find the time to provide actionable feedback to volunteers. This insight highlights an opportunity for improvement: by building in new, realistic approaches for meaningfully communicating and interacting with volunteers, officers may be able to supervise more effectively, and volunteers may receive more useful feedback.

We then mapped the challenges, insights, and opportunities to a diagram that mirrors the program’s planning and implementation process (Fig. 2). We then used this map as a starting point to design 20+ “prototype” intervention components to address user needs. These prototypes were put to the test in three focus group sessions with stakeholders (Fig. 1). Feedback from these sessions served to finalize the management intervention. The intervention consisted of a management training, feedback loops, communication tools, goal setting, and planning tools (Fig. 2).

#### Phase II: Experimental design

##### Baseline training and data collection

Both treatment and control groups were invited to a training in Abuja, Nigeria—two managers (or “officers”) from each organization. The control group training took place on August 3rd and 4th, 2017. Trainees received one electronic tablet per CBO with Qualtrics Survey Software [13] installed. During the training, the participants were introduced to the costing component of the study, and were trained on how to collect data through the Qualtrics platform. Specifically, participants learned how to collect basic facility information, monthly inputs (condoms, test kits, etc.) used for the interventions, staff working for the interventions and their salaries, monthly rent and utilities expenses, participation in trainings, and monthly outputs produced (number of FSW served by the interventions). They subsequently collected and uploaded retrospective data for the period January 2016 to July 2017 onto the survey platform.

The treatment group training took place between August 7th and 11th, 2017, and the content was the same as that of the control group, plus an additional 3 days of management training. Topics included financial, workplace, and personnel management. The management training was broadly focused around “lean management”, a conceptual framework for improving the quality and efficiency of service delivery through small and pragmatic shifts in management practices (see Additional file 1). The attendees were also given several “management tools”—designed through the qualitative formative research—to help with their daily work. These tools included: (1) a whiteboard calendar to help them organize their constantly changing schedules, (2) “pledges” to help clarify the role of each volunteer, (3) materials and support on how to solicit meaningful feedback from volunteers, and (4) phones and phone credit to allow staff to communicate more often and effectively with volunteers in the field. As with the control group, the treatment group collected baseline data from their CBO records dated between January 2016 to July 2017.

##### Prospective intervention and data collection

Throughout the course of the study, the treatment group will receive: (1) the aforementioned “management tools” (calendar, pledges, feedback loops, and phones); (2) additional monthly “follow up” trainings via an online platform; and (3) monthly reports about their “performance”, (i.e. the data they send about inputs, outputs, and costs) (Additional file 2). The data reports will include information regarding their monthly average costs and number of FSWs reached per intervention, as well as comparisons of their performance relative to their (anonymized) peers. The online platform will provide a space through which the participants can posts successes, challenges, and solutions. This report will allow them not only to observe their performance in a specific period of time, but also to analyze changes in these outcomes over time.

### Outcomes

Our primary outcome of interest is service delivery efficiency, as measured by the CBO-level average cost per service delivered, which is referred to as *unit cost*. Unit cost will be calculated for three services provided by the CBOs: (1) HIV testing and counselling, (2) HIV education, and (3) syndromic management of STIs.

#### Unit cost

Our goal in the project is to estimate the unit costs of three prevention interventions. In order to accomplish this, we will: (1) estimate the CBO-level total costs as the sum of the quantities of key inputs used to produce the interventions multiplied by their prices; and (2) divide the total costs by the total outputs produced per intervention, per CBO.

Inputs include staff salaries, supplies, rent, utilities, and trainings (Fig. 3). Supplies include condoms, lubricants, test kits, pamphlets, gift items or incentives. Prices will be collected from centralized records at the SFH headquarters office, and include prices of the various commodities the CBOs receive, staff salaries or payments by staff position or title, and information on trainings provided to the CBOs. Outputs include number of FSW tested, number of FSW tested positive, number of FSW educated, and number of FSW referred for STI treatment.

**Fig. 3 Fig3:**
[figure not shown]
Summary of measurement methods

First, total cost will be estimated for each intervention for 2016 by summing the products of each inputs category by their prices, as follows:1$$TC_{ci} = \mathop \sum \limits_{j = 1}^{j = 6} (s_{ijc} *P_{j} ) + \mathop \sum \limits_{k = 1}^{k = 4} W_{i} (l_{ikc} *S_{kc} ) + \mathop \sum \limits_{m = 1}^{m = 4} (vol_{imc} *S_{mc} *Srv) + \sum {W_{i} U_{ic} } + \sum {W_{i} T_{ic} }$$where TC_ci_ = Total costs of CBO c and intervention i, c = CBOs (n = 31), i = intervention, either 1. STI treatment, 2. HIV testing and counselling, or 3. HIV education, s_ij_ = number of supplies for each intervention i, supplies_ij_ = number of supplies for each intervention i1. 2. 3., j = supply category, 1. condoms, 2. lubricants, 3. test kits, 4. female condoms, 5. lubricants, 6. gift items (including toothbrush, toothpaste, playing cards, soap, toilet paper, etc.), P_j_ = Price of each supply j, l_ik_ = number of staff working on intervention i, by staff category k, k = staff category, 1. Executive director, 2. program officer, 3. monitoring and evaluation officer, 4. treatment program officer, etc. (varies slightly depending on program), S_k_ = annual salary paid to staff category k, vol_im_ = number of volunteers working on intervention i, by type of volunteer staff m, m = type of volunteer staff, including 1. peer educator, 2. counselor tester, and 3. venue outreach staff, 4. community facilitator (varies slightly depending on program), S_m_ = salary paid per type of volunteer staff services per service delivered, Srv = annual number of services provided by volunteer staff, W_i_ = Intervention weight, Ui_c_= Utilities costs, 
T_ic_ = Costs of training activities.

Since utilities and training activities are shared by all the facilities’ interventions, they will be allocated based on the proportion of clients per intervention (FSW) over the total number of CBO clients recorded for the same year (W), using the following formula:$$W_{ci} = \frac{{FSWc_{i} }}{{\mathop \sum \nolimits_{i = 1}^{3} FSW_{i} }} ;\;W \in \left( {0,{ 1}} \right].$$

Staff time is allocated to specific interventions depending on the type of staff. Volunteer staff mostly work on a single intervention, and so their full time will be allocated to their corresponding intervention. In contrast, managerial staff work on various interventions, and their time will thus be allocated applying the same weight as seen above.

In order to estimate the average annual cost per client or unit cost (UC), the total costs per intervention will then be divided by the total number of clients served by the same intervention (NC):$${\text{UC}}_{\text{ci}} = \frac{{TC_{i} }}{{FSW_{ci} }}.$$

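### Equation 1, the numerator of the primary outcome, does not match the protocol's own input list (no rent, lubricants twice, no pamphlets), and its volunteer term rests on an undefined service count

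*Protocol article*

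**What the plan says.** The Outcomes section of the protocol article makes CBO-level unit cost the primary outcome, for three services. The Unit cost section builds it as total cost (Equation 1) divided by clients served.

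The text before the equation declares the inputs: "Inputs include staff salaries, supplies, rent, utilities, and trainings". For supplies it says: "Supplies include condoms, lubricants, test kits, pamphlets, gift items or incentives". The sections on baseline training and on data collection methods both state that rent is collected.

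Equation 1 has five terms: supplies, weighted paid staff, volunteers, weighted utilities and weighted training. Its legend gives the supply index as "1. condoms, 2. lubricants, 3. test kits, 4. female condoms, 5. lubricants, 6. gift items". The shared-cost symbols are introduced with "W_i_ = Intervention weight, Ui_c_= Utilities costs", followed by training. The allocation rule begins: "Since utilities and training activities are shared by all the facilities’ interventions, they will be allocated based on the proportion of clients per intervention".

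The volunteer term is number of volunteers × pay per service × Srv, where "Srv = annual number of services provided by volunteer staff". The paid-staff term multiplies the weight W by salary and by the "number of staff working on intervention i, by staff category k". The text below the equation describes the weighted staff as managerial and working across interventions.

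**The concern.** A formula for the primary outcome should contain each declared input once and have consistent units. Equation 1 departs from the declared list in two places (rent and supplies), and one factor in a third term can be read in two ways that give very different answers. Two analysts who follow the text faithfully could compute different unit costs from the same data.

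Difference-in-differences cannot be relied on to remove this. Equation 2 models cost per client, and a fixed cost such as rent is spread over a client count that the intervention may change. The volunteer term has a similar weakness: if Srv is taken as a total, a change in the number of volunteers moves the measured cost even when pay and services stay the same.

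**Working it through.** The article gives no worked cost figure to reproduce. The check therefore compares terms, then uses algebra with assumed numbers, marked as such.

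**1. Declared inputs against Equation 1**

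- Salaries: present (staff and volunteer terms).
- Utilities: present (U).
- Training: present (T).
- Rent: no symbol. U is defined as utilities only, and the allocation sentence names only utilities and training.
- Condoms, test kits, gift items: present.
- Lubricants: present twice (categories 2 and 5).
- Pamphlets: absent.
- Female condoms: category 4, which can be read as part of condoms in the declared list.

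**2. Rent**

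The weight is W_i = FSW_i / ΣFSW. Allocated in the same way as utilities, rent R adds to the unit cost of service i

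W_i × R / FSW_i = R / ΣFSW,

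which is rent divided by all clients of the CBO.

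- *Level.* If rent is a share r of total cost, leaving it out shifts log unit cost by log(1 − r). Assumed r = 2%, 5%, 10%, 15% gives −0.02, −0.05, −0.11, −0.16.
- *Change over time.* If clients rise by 20% (assumed) and rent is constant, true rent per client falls from R/ΣFSW to R/(1.2 × ΣFSW), a saving of 1 − 1/1.2 = 1/6 of baseline rent per client. A formula without rent does not see this saving. With rent at 2% to 15% of unit cost, the hidden saving is 0.02/6 = 0.3% to 0.15/6 = 2.5% of baseline unit cost.

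**3. Lubricants**

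If both categories were filled with the same quantity, a lubricant share of 2% to 15% of total cost (assumed) would raise log unit cost by log(1.02) = 0.02 to log(1.15) = 0.14.

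**4. Volunteer term**

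Take 1,000 services paid at 1 unit each (assumed), so true pay is 1,000.

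- *Srv as a total:* volunteers × 1 × 1,000 gives 5,000, 10,000 or 20,000 with 5, 10 or 20 volunteers. The units are persons × money.
- *Srv as a mean per volunteer:* with 10 volunteers, 10 × 1 × 100 = 1,000, which is correct.

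On the first reading, going from 10 to 12 volunteers with services and pay unchanged moves the measured cost from 10,000 to 12,000. The legend's wording fits the first reading better, and the presence of a head count in the product fits the second. In the equation, Srv has no index for CBO, intervention or volunteer type, while the two factors beside it do.

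**5. Paid-staff term**

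The three weights sum to 1, so a post that covers all three services is recovered in full. With assumed client counts of 200, 800 and 1,000 (W = 0.1, 0.4, 0.5), a post covering only the first service would be recovered at 10%, and one covering the first two at 50%. This matters only if such posts exist.

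**The case against.** The best defence is that these are drafting slips in a loosely edited legend, which also defines the supply quantity twice. Category 5 may simply be a misprint for pamphlets, so the duplicate and the omission would be one error. Nothing suggests that anyone would enter lubricant quantities twice. Rent may be meant to sit inside U: the training section speaks of rent and utilities together, and the figure that the input list cites is not available here. The volunteer product is correct if Srv is per volunteer.

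Much of this stands as an explanation, but it does not repair the text. The input list names rent separately from utilities, U is defined as utilities, and the reader must guess at Srv.

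Three stronger readings are tempting and not supported:

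- *Volunteer cost is certainly inflated many times over.* This holds only if Srv is a total, which the article does not settle.
- *Part of some salaries is certainly lost.* The article describes the weighted staff as shared managers and documents no single-service salaried post. The treatment program officer title, and the statement that managers work on various rather than all interventions, are only hints.
- *Every unit cost is wrong, in a way that could pass for an intervention effect.* This takes the worst reading of each term. The intervention works on communication with volunteers and on their roles, but no planned change in head count is described.

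**Conclusion.** Equation 1 is wrong as written on rent and on the supply list: it departs from the protocol's own definition of the inputs to the primary outcome. The volunteer term is badly defined rather than proven wrong. The paid-staff term is a query only.

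The size of any effect on the treatment comparison is unknown, because the article gives no cost shares. Under the assumed shares, the rent and supply slips are modest. The volunteer term has the potential to be large, but only if Srv is used as a total. Constant errors would partly cancel in the difference-in-differences. Rent per client would not cancel if client numbers change differently by arm. Equation 1 is stated for 2016 and no other formula is given for endline; the assessment assumes that the same formula is used at both times.

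**What to change.** Before unit costs are computed, restate Equation 1 and its legend as follows:

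- Add a rent term allocated by W in the same way as utilities, or define U as rent plus utilities.
- List lubricants once and add pamphlets.
- Replace the volunteer term with Σ_m S_mc × Srv_imc, where Srv_imc is the number of services delivered by volunteer type m for service i in CBO c. Alternatively, keep the head count and define Srv explicitly as services per volunteer, with the same indices.
- State that the same formula applies at baseline and endline.
- Confirm whether every salaried post covers all three services. If any covers fewer, rescale W over the services that the post covers so that its weights sum to 1.

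The cost is a revision of the text and the analysis code. Rent is already collected. Services by volunteer type are not listed among the collected items (the outputs listed are FSW served, by intervention), so the sponsor should check whether they can be derived from those counts. Pamphlet quantities and prices should be checked in the same way.
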